## Abstract

**Background:**

Aging is an irreversible process shaped by genetic and environmental factors. Beyond physical and mental decline, it involves complex biological mechanisms. Programmed theories propose aging follows a biological clock, while error theories attribute it to environmental damage. A key mechanism is telomere shortening; once critically shortened, cells enter senescence. Telomerase preserves telomeres, but its activity decreases with age. Aging also causes cognitive decline, measurable through tools like electroencephalography (EEG).

**Study design:**

This two-arm, double blind, placebo-controlled superiority randomized controlled trial evaluates the effects of *Bacopa monnieri* freeze-dried herbal decoction (BMFD) on aging and cognition. Elderly participants (MoCA ≥24) will be randomized to receive BMFD or placebo, administered as 120 mL twice daily for 45 days, with assessments at baseline, 45, and 90 days. Conducted at the Clinical Trial Center, Faculty of Indigenous Medicine, University of Colombo, the trial tests BMFD’s ability to stabilize aging processes and enhance neurocognitive functions.

**Outcomes:**

Primary outcomes include telomerase activity and telomere length (qPCR). Secondary outcomes include neurocognitive function [validated MoCA for the Sri Lankan population], neurophysiological functions—nerve conduction test (NCT) for upper and lower limb nerves and brain electrical activity (EEG)—and assessing health-related quality of life (HRQoL) using a validated questionnaire.

**Discussion:**

This trial will provide evidence on BMFD’s potential to preserve telomere length, support cognitive functions, and slow aging processes. Integrating Ayurvedic principles, including constitution (*Prakriti*), it aims to enable early detection of cognitive decline and aging-related changes. Findings are expected to inform preventive and personalized strategies, contributing to evidence-based applications of *Bacopa monnieri* in healthy aging.

**Clinical trial registration:**

https://doi.org/10.1186/ISRCTN64126920, identifier ISRCTN64126920.

## Introduction

### Aging: a multifactorial and irreversible process

Aging is an irreversible, multifactorial process influenced by both intrinsic (genetic) and extrinsic (environmental) factors, contributing to individual variability in longevity (1, 2). It is not merely a decline in bodily functions but a complex mechanism. Theories of aging include programmed theories, which suggest regulation by biological clocks, and error theories, attributing aging to gradual accumulation of DNA damage, free radicals, and macromolecular cross-linking (2). Cellular senescence, resulting from telomere shortening (replicative senescence) or cell stress (cellular senescence), is closely associated with aging (2). Recent studies indicate that aging cannot be captured by a single biomarker and requires integrative assessment of biological, functional, and behavioral parameters. A multicenter frailty-detection study using machine-learning approaches emphasized the importance of combining molecular and functional markers for predictive modeling (3), aligning with the present protocol’s evaluation of telomere biology, neurocognitive function, electrophysiology, and constitution (*Prakriti*).

### The role of telomeres in aging

Telomeres are specialized structures at the ends of chromosomes, composed of clusters of G residues (4). They maintain chromosomal stability by ensuring complete replication of DNA during cell division (5). Telomeres shorten with each division, leading to replicative senescence. Critically short telomeres result in chromosome degradation and progressive genetic loss. Telomerase, a specialized enzyme, helps maintain telomere length and prevent cellular senescence (6–8). Despite its importance, telomerase activity declines with age (9–12) and is often undetectable in many human cells, though it remains measurable in germline cells, cancer cells, and actively dividing peripheral blood mononuclear cells (13–15).

### Aging and *Prakriti*

*Prakriti*, or a person’s tridosha-based constitution, influences susceptibility to chronic diseases (16–18). While well-established in Ayurveda, modern science increasingly recognizes these links. Disease risks can be predicted based on body types: *Kapha*-dominant individuals are prone to weight gain and metabolic syndrome (heart disease, hypertension, diabetes); *Pitta*-dominant individuals to ulcers, bleeding disorders, and skin conditions; *Vata*-dominant individuals to neurological issues, dementia, movement and speech disorders, arrhythmias, and related chronic diseases (19–24). Classical texts suggest *Vata* types have the highest overall disease risk. Long-term cohort studies also show that environmental and climatic factors influence chronic physiological processes and pain sensitivity with age (25), aligning with Ayurveda’s recognition of individual variability in response to environmental stressors, metabolism, and aging.

### Cognitive decline in aging

Aging is often accompanied by cognitive decline. Synchronous neural firing, generating rhythmic brain oscillations, can be measured with scalp EEG (26–28). Parameters such as power, peak frequency, and phase correlate with neurocognitive functions (29–31). Changes in these oscillatory parameters with age provide insights into the evolution of cognitive function over time (32).

### Health implications of aging

Increased life expectancy poses challenges related to age-associated health issues. Common causes of death in older adults include respiratory diseases, heart disease, cancer, and stroke, while chronic conditions such as arthritis, diabetes, osteoporosis, Alzheimer’s disease, depression, Parkinson’s disease, and age-related urinary problems are prevalent (33). Approximately two-thirds of daily global deaths (~150,000) are age-related (34). The growing elderly population (≥65 years) increases strain on healthcare systems, pension funds, and the workforce, with regional disparities further compounding these challenges (35, 36).

### Sensory and motor impairments in aging

Peripheral neuronal weakening in aging affects sensation, muscle strength, balance, and gait. Declining nerve transmission reduces tactile sensitivity and contributes to visual and hearing impairments. Reduced neuromuscular efficiency weakens coordination, shortens reaction times, and increases the risk of falls and mobility issues. Assistive devices can partially compensate, but age-related motor and balance decline remain challenging. Neurological diseases such as Parkinson’s disease can accelerate deterioration. An individual-participant meta-analysis showed that quantitative sensory and neurophysiological markers strongly predict outcomes in chronic degenerative conditions (37), supporting the use of nerve conduction studies and EEG in this trial to capture age-related changes in neuroplasticity and neural efficiency relevant to cognitive aging.

### The role of *Bacopa monnieri* in cognitive health

*Bacopa monnieri*, a traditional Ayurvedic herb, has long been used to enhance memory, learning, and overall cognitive function. It also exhibits sedative and anti-epileptic properties (38). Despite its historical use, scientific evidence on *Bacopa monnieri* decoctions, such as BMFD, for stabilizing aging and cognitive decline is limited. While memory-enhancing effects are recognized, there is no definitive evidence on its impact on telomerase activity, telomere length, or neurocognitive functions in older adults (39). Telomerase activity and telomere length can be measured in blood mononuclear cells, whereas cognitive function requires neuropsychological assessment. Recent studies indicate that gut microbiota composition and tryptophan-derived metabolites influence neuroinflammation, pain regulation, and cognition via the gut–brain axis (40). *Bacopa monnieri*’s antioxidative, anti-inflammatory, and neuroprotective properties may underlie its potential effects on telomere stability and cognitive resilience in aging adults.

### Research gaps and study purpose

This study aims to evaluate the potential of BMFD decoction in stabilizing aging and influencing neurocognitive functions in the elderly. Evidence on its effects on telomerase activity, telomere length, and age-related cognitive changes—particularly in relation to Deha Prakriti (body constitution)—is limited. By examining these effects, this study seeks to explore how BMFD may support healthy aging and neurocognitive functions, contributing to personalized interventions, including dietary, lifestyle, and herbal strategies, to mitigate cognitive decline and enhance overall well-being.

## Methods

### Study design

This is a two-arm, open-label, non-inferiority randomized controlled clinical trial that will be conducted at the Clinical Trial Center, Faculty of Indigenous Medicine, University of Colombo, Sri Lanka. The test product will be BMFD, a freeze-dried formulation of *Bacopa monnieri*. The trial will evaluate the effects of the *Bacopa monnieri* herbal supplement on aging, neurocognitive functions with relation to Constitution (*Prakriti*), and constitution (*Prakriti*) in healthy adults, compared to a placebo. Participants with (the MoCA score of 24 or above) will be randomly assigned to one of two arms following a 1-week run-in period, with the BMFD herbal supplement administered orally for 45 days. This study protocol has been developed in accordance with the Standard Protocol Items: Recommendations for Interventional Trials (SPIRIT) guidelines. Ethics approval has been obtained from the Ethics Review Committee, Faculty of Indigenous Medicine (ERCFIM), University of Colombo, Sri Lanka (ERC-23/202). The trial is registered in the ISRCTN registry under trial number ISRCTN64126920 https://doi.org/10.1186/ISRCTN64126920.

### Study setting

The study will be conducted at the Clinical Trial Center, Faculty of Indigenous Medicine, University of Colombo, Sri Lanka. Participants will be recruited from healthy individuals, with the MoCA score of 24 or above. Recruitment will take place through a newspaper advertisement inviting individuals to participate in the trial at the Clinical Trial Center, Faculty of Indigenous Medicine, University of Colombo.

### Participants

Participation in this research project is voluntary. Participants will be recruited through a screening process to assess eligibility based on inclusion and exclusion criteria. Eligible individuals will then be randomly assigned to either the BMFD decoction group or the placebo group.

### Inclusion and exclusion criteria

The inclusion criteria include: (1) healthy individuals aged between 60 and 64 years at the time of enrollment, of either sex; (2) nonsmokers and non-alcoholic; (3) the MoCA (the Montreal Cognitive Assessment) score of 24 or above. Participants will not be permitted to take any other medications during the trial period. If they need to take any additional medication, they must notify the investigators and withdraw from the trial. The exclusion criteria include: (1) individuals with Chronic diseases, e.g., Kidney Disease, Cardiovascular Disease, Liver disorders, psychiatric illnesses, Diabetes Mellitus, cancers, Hypertension, hyperlipidemia; (2) participants with dyspeptic symptoms; (3) those with reduced capacity to complete the tasks involved in the study.

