### Sample size

The primary outcomes of this clinical trial are telomere length, measured in kilobases using quantitative PCR, and telomerase activity, quantified using an ELISA-based TRAP assay. Both are continuous biological markers that reflect cellular aging processes. Sample size estimation was conducted using the formula for comparing two independent means, appropriate for continuous outcomes. Based on pilot findings reported by Ornish et al. (41), a mean difference of 0.5 kb in telomere length between groups was considered clinically relevant, with a standard deviation (SD) of 0.7 kb. A significance level of *α* = 0.05 and power of 80% (*β* = 0.20) were applied in the calculation. Using these parameters, the required sample size per group was obtained, and after accounting for a 10% dropout rate, the final required sample size was determined to be 37 participants per group, resulting in a total of 74 participants for the study. Although Ornish et al. (41) studied men with prostate cancer—a different population from our healthy older adults—we used this data as it provided the most relevant preliminary estimate of variability and effect size available. We acknowledge that this may limit the precision of our sample size calculation and will interpret our findings accordingly. With a significance level of *α* = 0.05 and power of 80% (*β* = 0.20), the required sample size per group was calculated, and after accounting for a 10% dropout rate, the final sample size was determined to be 37 participants per group, for a total of 74 participants. To further strengthen the validity of these assumptions, a dose-finding and feasibility phase will be conducted prior to the full RCT. Data generated from this phase will be used to validate and refine the expected effect sizes, particularly for telomerase activity and cognitive outcomes, thereby enhancing the robustness of the final trial estimates.

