### Recruitment

Individuals interested in participating in this clinical study will receive a detailed Patient Information Leaflet (PIL), which will be accompanied by a verbal explanation of the study procedures. If participants agree with the information provided in the PIL, they will then complete a screening questionnaire. Written informed consent will be obtained from each participant by the investigators prior to the initial interview. During the initial interview, participants will undergo a comprehensive history taking, physical examination, and various hematological and biochemical investigations (including FBS, FBC, ESR, ALT/AST, serum creatinine, and UFR). Recruitment based on MoCA analysis score [the MoCA score of 24 or above (42–47)]. Participants who meet the inclusion and exclusion criteria will be recruited for the study. All baseline assessment forms [including the MoCA analysis form, *Prakriti* analysis (constitution), Quality of Life questionnaire] will be completed by the investigators. Participants will not be permitted to take any other medications during the trial period. If they need to take any additional medications, they must inform the investigators and discontinue participation in the trial.

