### Randomization

The randomization sequence will be generated using an online randomization tool.^1^ Block randomization will be applied with blocks of 12 to create a randomization schedule for 74 participants. Patients will be assigned to treatment groups based on the generated sequence. A one-week supply of the assigned investigational product will be distributed to the patients according to their random allocation. The allocation ratio will be 1:1 for each group. Each randomization number’s corresponding allocation will be placed into individually sealed, opaque envelopes. These envelopes, along with the allocation sequence, will be securely stored by an investigator who is not involved in participant recruitment. Participants who meet the inclusion and exclusion criteria will be enrolled in the study and assigned a randomization number sequentially, based on the date and time of their recruitment. The treatment indicated in the sealed envelope for each number will then be provided to the corresponding participant. A flowchart depicting the study design is presented in Figure 1.

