### Method of data analysis

For both primary and secondary outcome measures, mean values at baseline and study completion, as well as mean differences, will be compared across the two study arms using ANOVA (Analysis of Variance) or the non-parametric Kruskal–Walli’s test, depending on the data’s normality. Within each treatment arm, changes in primary and secondary outcomes before and after the intervention will be analyzed using either paired-sample *t*-tests or the non-parametric Wilcoxon signed-rank test, based on the distribution of the data. For all normally distributed outcomes, 95% confidence intervals will be calculated. Categorical variables will be analyzed between groups using the Chi-square test. Potential confounding factors will be adjusted using ANCOVA, with adjusted mean values and corresponding confidence intervals subsequently calculated and reported. Regarding missing data, instead of the last observation carried forward, multiple imputation techniques will be employed to handle missing outcome data, ensuring a more robust and unbiased estimation. Statistical analysis will be conducted using the SPSS software (version 20.0), and the level of significance will be set at *α* = 0.05. In cases of missing outcome data, the most recent available values of the outcome measures will be used as replacements. Intention-to-treat analysis will be applied for all efficacy and safety outcomes. Additionally, per-protocol analysis will be conducted for efficacy outcomes, including only participants who complete the follow-up.

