### Statistical analysis

The statistical analysis plan has been developed to align with the study objectives and ensure rigorous evaluation of outcomes. Descriptive statistics will be used to summarize baseline characteristics across study arms. Continuous primary and secondary outcomes will be assessed for normality prior to analysis. Between-group comparisons of mean changes from baseline to study completion will be conducted using analysis of variance (ANOVA) for normally distributed data or the Kruskal–Wallis test for non-normal data. Within-group pre–post changes will be analyzed using paired-sample *t*-tests or Wilcoxon signed-rank tests, as appropriate.

To account for baseline imbalances and potential confounding factors such as age, sex, and baseline outcome values, analysis of covariance (ANCOVA) will be applied, with adjusted mean differences reported alongside 95% confidence intervals. Categorical variables will be compared between groups using the Chi-square test or Fisher’s exact test, as appropriate.

Missing outcome data will be handled using multiple imputation methods to minimize bias and improve the robustness of estimates. The primary analysis will follow the intention-to-treat principle for all efficacy and safety outcomes, with a secondary per-protocol analysis conducted for efficacy outcomes among participants who complete the follow-up assessments. All statistical analyses will be performed using SPSS software (version 20.0), with a two-sided significance level set at *α* = 0.05.

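### The rule that anyone needing another medicine must leave the trial is not reconciled with intention-to-treat: it replaces observed outcomes with imputed ones for people selected by a health event after randomisation

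*Protocol article*

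**What the plan says.** The rule appears twice in the protocol article. Under Inclusion and exclusion criteria: "If they need to take any additional medication, they must notify the investigators and withdraw from the trial". Under Recruitment: "If they need to take any additional medications, they must inform the investigators and discontinue participation in the trial". Neither statement limits the type or duration of the medicine. Both refer to the trial as a whole and not to the study product, and no section describes assessments after such a withdrawal.

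The Statistical analysis section says: "The primary analysis will follow the intention-to-treat principle for all efficacy and safety outcomes". Method of data analysis says the same in substance. On missing outcomes, Statistical analysis names multiple imputation. Method of data analysis first names multiple imputation in place of last observation carried forward, and a few lines later says that a missing outcome is replaced by the latest value on record.

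The secondary analysis is described as follows: "per-protocol analysis will be conducted for efficacy outcomes, including only participants who complete the follow-up". Statistical analysis repeats this definition.

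Safety monitoring and stopping criteria works differently. There, a serious adverse event judged related to the product ends that participant's use of the product; leaving the trial is not mentioned.

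**The concern.** Needing a medicine is a health event that occurs after randomisation. If it ends participation, the people lost are not a random subset: they became ill, had a symptom or had an adverse event. Their later telomere, cognitive and quality-of-life results have to be imputed, and imputation under missing-at-random cannot be checked against data that were not collected. If the need for medicine differs by arm, the comparison is biased.

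Safety is affected too. The Safety assessment section promises care for a reaction that leads to hospital admission. Such care will usually involve a medicine, which under the eligibility rule removes the person from the trial. The participants who matter most for safety could then miss the laboratory tests after the intervention, and drop out of the between-arm comparison that the monitoring board is asked to watch.

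Loss also costs power, and the sample size allows for 10% dropout only.

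**Working it through.** **1. The passages side by side.**
- Eligibility and Recruitment: another medicine means leaving the trial.
- Safety monitoring: a related serious event means stopping the product.
- Both analysis sections: everyone randomised is analysed, for efficacy and safety.

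Intention-to-treat needs outcomes on everyone randomised. The first rule stops their collection for one group and leaves imputation to fill the gap.

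**2. What imputation would do.** The Primary outcomes section measures telomere length and telomerase activity at baseline, 45 and 90 days. Table 2 ticks them at baseline and week 12 only. On the Table 2 schedule, the latest value for anyone who leaves before week 12 is the baseline, so carrying it forward imputes a change of zero. If a share p of each arm is treated this way, and leavers would otherwise have resembled stayers, the planned difference of 0.5 kb shrinks to (1 − p) × 0.5:
- p = 10%: 0.45 kb
- p = 20%: 0.40 kb

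Multiple imputation would give a different answer from the same data, so which of the two sentences governs matters.

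**3. The plan's own sample size.** Inputs:
- Sample size section: "a mean difference of 0.5 kb in telomere length between groups was considered clinically relevant, with a standard deviation (SD) of 0.7 kb" and "power of 80% (*β* = 0.20) were applied in the calculation"
- Statistical analysis section: "with a two-sided significance level set at *α* = 0.05"
- Randomization section: "The allocation ratio will be 1:1 for each group"

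n per group = 2 × [SD × (1.960 + 0.842) / difference]² = 2 × [0.7 × 2.802 / 0.5]² = 30.8, so 31. The exact t-test needs 32. Dividing by 0.9 for 10% dropout gives 34.4 (35) or 35.6 (36). The stated 37 is within two of either, and follows exactly from 33 / 0.9 = 36.7. The figure is reproduced, with slight slack.

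**4. Power at other losses.** Two-sided t-test, standardised difference 0.5 / 0.7 = 0.714, 37 randomised per group, leavers contributing no information:

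| Total loss (assumed) | 37 × (1 − loss) | Completers used | Power |
|---|---|---|---|
| 10% | 33.3 | 33 | 81.5% |
| 15% | 31.4 | 31 | 79.0% |
| 20% | 29.6 | 29 or 30 | 76.2% or 77.6% |
| 30% | 25.9 | 25 or 26 | 69.7% or 71.4% |

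Power stays at 80% with 32 completers (80.3%), a loss of 5/37 = 13.5%. The normal approximation still gives 80.9% at 15% loss.

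**5. What rate of medicine use would matter.** With a constant weekly withdrawal rate r for medicine alone (assumed), loss by day 90 is 1 − (1 − r)^(90/7):
- r = 1%: 12%
- r = 2%: 23%
- r = 3%: 32%

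The whole 10% is used at r = 1 − 0.9^(7/90) = 0.8% per week.

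**6. Per-protocol set.** The only stated criterion is completing follow-up. A participant who attended every visit but took little or no product would qualify.

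**The case against.** Several stronger readings are tempting, and the document does not support them.

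- *That the rule contradicts intention-to-treat outright.* It does not. The plan names multiple imputation, which formally keeps withdrawn participants in the analysis set. The weakness is reliance on imputed values where observed ones could be had.
- *That losses will exceed 10%.* No rate of medicine use is given, the 10% is not split by cause and may already include these withdrawals, and the trial admits healthy people aged 60 to 64 without chronic disease. The sample size also tolerates about 13–15% loss.
- *That the missingness differs by arm.* Excluding people with dyspeptic symptoms does not show that the product causes gut complaints. A difference by arm is a plausible risk, not a documented fact.
- *That the article says no data are collected after withdrawal.* It is silent. A condensed article may leave such procedures to the full protocol, and the safety section speaks of monitoring for the whole study. This softens the point but does not remove it: the two statements of the rule say that the person leaves the trial, and nothing in the article qualifies them.

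It can also be said that the per-protocol set is secondary and that adherence thresholds usually belong in an analysis plan. That is fair, and it makes this a minor point; but the article does state a definition, twice, and the definition is completion alone.

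Finally, the power figures come from an unadjusted t-test, whereas the plan also uses ANCOVA with baseline values. They indicate scale only.

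**Conclusion.** The concern holds as a failure to reconcile the withdrawal rule with the analysis. As written, the plan gives up later outcome and safety data on participants selected by a post-randomisation health event. It then relies on imputation under a doubtful missing-at-random assumption, with two incompatible rules for doing it.

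The size cannot be fixed from the document. The loss may differ by arm and may exceed the allowance. Under assumed losses, power is about 82% at 10%, 76–78% at 20% and 70–71% at 30%. The bias argument does not need the 10% to be exceeded: it turns on who is lost, not only on how many. The completers-only per-protocol set is a secondary point. The change should be made before recruitment, but the point does not invalidate the design.

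**What to change.** Reconcile Inclusion and exclusion criteria and Recruitment with Safety monitoring and stopping criteria and with both analysis sections, so that medication or treatment status does not end follow-up:

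1. State that all randomised participants keep the scheduled day 45 and day 90 outcome and safety assessments unless they withdraw consent, that other medicines are recorded, and that everyone is analysed as randomised. Whether and when study product is stopped is left to the sponsor.
2. Delete the last-value replacement sentence in Method of data analysis, so that multiple imputation is the single rule. Align Table 2 with the Primary outcomes section on when the telomere measures are taken.
3. Define the per-protocol set by completed follow-up, no major deviation and a pre-stated level of adherence, using pack counts at the existing weekly visits.

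The cost is wording in the protocol and consent documents, an ethics and registry update, and a few more completed visits that are already on the schedule. The small downside is that some observed outcomes will reflect another medicine.
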